### Treatment

Participants who are randomised to arms 1 and 2 will receive the standard of care regimen: rifampicin plus isoniazid once daily for 90 doses (3HR).

Participants who are randomised to arms 3 and 4 will receive rifapentine plus isoniazid once weekly for 12 doses (3HP) and those who are randomised to arms 5 and 6 will receive rifapentine plus isoniazid once daily for 28 doses (1HP). Participants will be given a 1-month supply of the medications at every visit in general but it also depends on local practice as this is a pragmatic trial.

In order to account for missed doses and interruption of treatment due to adverse events, participants given 3HR or 3HP will have 16 weeks and those given 1HP will have 6 weeks to complete treatment. In the study by Swindells *et al*, participants were given 8 weeks to complete 1HP.^18^ We have chosen 6 weeks to make the period proportionally similar to that for 3HR and 3HP. Clinicians will assess the need for treatment extension based on the assessment of adherence and review of reasons for non-adherence but should not extend beyond recommended grace periods.

In all arms, participants will receive vitamin B_6_ (pyridoxine). The dosages of study drugs are shown in table 1.

**Table 1 T1:** Doses of study treatment

	Body weight		
Arm 1 and 2: rifampicin plus isoniazid once daily for 90 doses (3 months)	<50 kg	≥50 kg	
	3 x Isoniazid/Rifampicin fixed dose combination (150/100)	2 x Isoniazid/Rifampicin fixed dose combination (300/150)	
Arm 3 and 4: rifapentine plus isoniazid once weekly for 12 doses (3 months)	30 to <32 KG	32 to <50 kg	≥50 kg
	Rifapentine 600 mg + Isoniazid 15 mg/kg	Rifapentine 750 mg + Isoniazid 15 mg/kg	Rifapentine 900 mg + Isoniazid 15 mg/kg (900 mg maximum)
Arm 5 and 6: rifapentine plus isoniazid once daily for 28 doses (1 month)	30 to <35 kg	35 to ≤45 kg	≥45 kg
	Rifapentine 300 mg + 300 mg Isoniazid	Rifapentine 450 mg + 300 mg isoniazid	Rifapentine 600 mg + 300 mg isoniazid

Rifapentine and rifampicin are known to induce the hepatic cytochrome CYP450 enzyme system. Caution is recommended in using medications that are metabolised by this system. Concurrent use of protease inhibitors, hepatitis-C antiviral drugs, or praziquantel is not permitted.

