### Outcomes

#### Primary outcome

The primary outcome is adequate treatment adherence, defined as taking ≥90% of allocated doses within the allowable time frame from randomisation (binary outcome). For the primary analyses, treatment adherence is measured using an electronic monitor box

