### Trial status

The trial has not yet started recruitment. We expect to start recruitment on 1 September 2022 and the trial will close when all participants have completed follow-up (ie, 12 months after initiation of treatment), record linkage to ascertain TB has been finished, and after the trial database is locked, which is anticipated to be within 3 months after information on primary and secondary outcomes have been collected.

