### Protocol version and date

This protocol is an abbreviated version of the protocol V.3.0, October 2020.

10.1136/bmjopen-2021-057717.supp1Supplementary data

10.1136/bmjopen-2021-057717.supp2Supplementary data

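### Table 1 puts a 45 kg participant in two 1HP weight bands with different rifapentine doses (450 mg and 600 mg)

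*Protocol article*

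**What the plan says.** The Treatment section of the protocol article refers the reader to Table 1 for the study drug doses. The row concerned is "Arm 5 and 6: rifapentine plus isoniazid once daily for 28 doses (1 month"). Its three weight bands are printed as "30 to <35 kg 35 to ≤45 kg ≥45 kg".

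The lowest band carries 300 mg of rifapentine. The middle band carries "Rifapentine 450 mg + 300 mg isoniazid" and the top band "Rifapentine 600 mg + 300 mg isoniazid". Isoniazid is 300 mg daily in all three, so only the rifapentine dose depends on weight.

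The only weight limit among the exclusion criteria in Box 1 is below 30 kg, so a person of 45 kg can be enrolled.

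**The concern.** The middle band closes at 45 kg with ≤ and the top band opens at 45 kg with ≥. Read literally, 45 kg belongs to both, and the table gives two daily rifapentine doses for the same person. The article has no tie-break rule and no other statement of the 1HP dose by weight.

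What is at stake is consistent dosing of an experimental regimen. The trial expects 15 sites, and two sites that each followed the printed table faithfully could treat identical participants differently. The secondary safety outcomes include Grade ≥3 adverse events and permanent discontinuation for adverse reactions, so the rifapentine dose is not irrelevant to what the trial measures.

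**Working it through.** **1. Does each weight have exactly one dose?** The bands below are from Table 1.

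| Regimen | Cut-point | Lower band ends | Upper band begins | Boundary weight falls in |
|---|---|---|---|---|
| 3HR | 50 kg | <50 | ≥50 | upper band only |
| 3HP | 32 kg | <32 | 32 | upper band only |
| 3HP | 50 kg | <50 | ≥50 | upper band only |
| 1HP | 35 kg | <35 | 35 | upper band only |
| 1HP | 45 kg | ≤45 | ≥45 | **both bands** |

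Four of the five cut-points are clean, and 45 kg for 1HP is the exception. Checking every weight from 30.0 to 119.9 kg in 0.1 kg steps gives the same answer. As printed, 45.0 kg is the only 1HP weight that matches more than one band, and the 3HR and 3HP rows have no overlap or gap. With the middle 1HP band ending at <45 kg, the 1HP row also has none.

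**2. How far apart are the two doses at 45 kg?**

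- Middle band: 450 / 45 = 10.0 mg/kg/day
- Top band: 600 / 45 = 13.3 mg/kg/day
- Ratio: 600 / 450 = 1.33
- Over 28 doses: 28 × 450 mg = 12.6 g against 28 × 600 mg = 16.8 g

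**3. Is either dose out of line with neighbouring weights?**

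- 300 mg band: 300 / 30 = 10.0, falling towards 300 / 35 = 8.6 mg/kg
- 450 mg band: 450 / 35 = 12.9, falling to 450 / 45 = 10.0 mg/kg
- 600 mg band: 600 / 45 = 13.3 mg/kg, and 600 / 45.1 = 13.3 just above the cut-point

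From 30 kg to just above 45 kg the regimen therefore runs from about 8.6 to about 13.3 mg/kg whichever sign is corrected. The upper limit arises at the cut-point itself. This shows only that both doses agree with those of adjacent weights; it does not show which is right.

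**4. How many participants could be affected?** The allocation ratio is 5:5:6:6:6:6, which sums to 34, so Arms 5 and 6 together hold 920 × 12 / 34 = 324.7 participants. The article gives no weight distribution, so the following is assumed: normal weights with mean m of 60 to 75 kg and SD s of 12 to 15 kg. If weight is recorded to the nearest 2h kg,

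expected number at 45 kg = 324.7 × [Φ((45 + h − m)/s) − Φ((45 − h − m)/s)].

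| Mean, SD (kg) | Whole-kg recording (h = 0.5) |
|---|---|
| 60, 15 | 5.2 |
| 60, 12 | 4.9 |
| 65, 12 | 2.7 |
| 70, 14 | 1.9 |
| 75, 15 | 1.2 |
| 75, 12 | 0.5 |

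With recording to 0.1 kg (h = 0.05) the range is 0.05 to 0.52.

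**5. Does it reach the primary analysis?** The primary outcome is "taking ≥90% of allocated doses within the allowable time frame from randomisation". A dose counts once whether it contains 450 mg or 600 mg, so the endpoint definition, the sample size and the power do not depend on the overlap.

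**The case against.** The strongest reply is that this is a defect of a journal table and not shown to be one of the trial's dosing instructions. The article states: "This protocol is an abbreviated version of the protocol V.3.0, October 2020". Sites would be expected to dose from the full protocol and the pharmacy documents, which may be correct. That stands as a limit on what can be concluded. It does not clear the table: condensing a protocol explains what an article leaves out, not something it prints wrongly.

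A second reply is that the intended reading is evident. All four other cut-points place the boundary weight in the upper band, so most readers would take <45 kg to be meant and give 600 mg. That is probably right, but the article does not say so, and a dosing table should not need the inference.

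A third is that the consequence is small and the headcount rests on assumed weights. Both points are correct. The range from 0.05 to 5.2 participants spans two orders of magnitude and serves only to show that the number is small.

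**Conclusion.** The table is wrong as printed: at exactly 45 kg the 1HP row returns two rifapentine doses, 10.0 and 13.3 mg/kg/day, and the article offers no way to choose between them. That conclusion follows from the printed symbols alone and needs no assumption.

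The severity is minor. One recorded weight is affected, and isoniazid is not. Under the assumed weight distributions, about five participants at most would be recorded at that weight, and fewer than one if weight is recorded to 0.1 kg. The primary comparison does not change. The article also reports: "The trial has not yet started recruitment", with a start expected on 1 September 2022, so there is no sign that anyone was dosed from the overlap. Whether the full protocol V.3.0 carries the same error cannot be determined from the article.

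**What to change.** Compare the 1HP row of Table 1 with protocol V.3.0 and the pharmacy documents, and make the bands mutually exclusive wherever the overlap appears.

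- Preferred form, matching the rest of the table: 30 to <35 kg, 35 to <45 kg, ≥45 kg. A 45 kg participant then receives 600 mg.
- If the sponsor's clinical team confirms that 450 mg is intended at 45 kg, keep the middle band and change the top band to >45 kg.
- If V.3.0 is already unambiguous, correct only the published table.

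The cost is one inequality sign and one document check before recruitment begins. The sample size, power and analysis are untouched.

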### Treatment support

#### Routine treatment support

Participants allocated to arms 1, 3 and 5 will receive routine treatment support. Participants will be given information about treatment for LTBI including expected adverse events and the importance of adherence, according to local practice. Adherence will be reviewed at each follow-up visit or remote consultation via self-reporting and/or pill count and discussed with the participant. An electronic pill monitor box, Wisepill EvriMed1000 (Wisepill, Somerset West, South Africa)^22^ will collect the date and time of each opening to collect information on adherence. However, it will be set to silent mode and not be used as an adherence reminder tool.

#### Intervention

Participants assigned to arms 2, 4 and 6 will receive a PAPA-based intervention designed to provide additional treatment support (ie, in addition to routine treatment support).^11^ Specifically, the intervention will consist of an animation which will (1) provide a rationale for treatment necessity and help people understand how LTBI treatment can help them to achieve a health goal that is important to them, (2) address common concerns about LTBI treatment and (3) address practical barriers to treatment (eg, anchoring treatment to daily activities). The animation will be supported by a leaflet that covers misperceptions about LTBI testing and treatment, and other frequently asked questions. Participants will also be asked to set reminders using an electronic pill monitor box (Wisepill EvriMed). The electronic pillbox allows two modes of reminders: audio alarm from the box or text-message to participants’ mobile phones.

The reminder can be set at prespecified times and can also be activated to send a reminder when the pill box is not opened. Site staff will discuss options with each participant and set reminders according to their preferences. Participants can opt not to receive reminders before or at the time of intended medication intake. However, they will still be reminded when the box is not opened within a pre-specified time in a day and they will receive a supportive text message automatically sent by the pillbox. The mode of reminder can be further adjusted during the course of treatment as necessary on discussion with a clinician. The pillbox will electronically collect the date and time of each opening.

### Study assessment and follow-up

#### Screening, randomisation and baseline assessment

Randomisation and baseline assessment will occur on the same day (week 0). In some cases, this may also be the same day as Screening. Following informed consent procedures, participants will be screened for eligibility. A TB symptom screen and urine pregnancy test will be carried out, and data on the participant’s TB risk group category will be collected. Demographic and medical history information will be collected. We will check the results of clinical, laboratory and radiological assessments performed under routine care before entry to the trial to confirm eligibility. A TB symptom screen and urine pregnancy test will be repeated at the randomisation/baseline visits unless the screening and randomisation visits occur on the same day.

#### Assessment of adherence

Assessment of adherence will be primarily measured using the Wisepill, which collects the date and time of each opening. Adherence will also be measured through self-reporting and pill count under routine care either at physical clinic visits or remote consultations as per the local standard. Attending clinicians will count the number of remaining tablets. The difference between the number of tablets dispensed and the number returned will be calculated.

#### Clinical assessment during follow-up

As per usual practice, liver function tests (hepatic transaminases, alanine aminotransferase/aspartate aminotransferase and total bilirubin) will be performed at week 2 for all participants. Afterwards, liver function tests will be performed at weeks 4, 8, 12 and 16 while on treatment and at completion, or at other times if deemed necessary by attending clinicians (eg, abnormality in preceding tests, new onset of symptoms suggesting potential liver toxicity). These tests should be performed at any time during the treatment and post-treatment phase if the participant exhibits symptoms or signs of drug-induced liver injury.

Adverse events expected with study drugs will be clinically assessed at every visit. These include anorexia, nausea, vomiting, fatigue, weakness, jaundice, rash, peripheral neuropathy and bruising. Participants who already completed treatment and have no scheduled visits will be given a phone call at week 8, 12, 16 and 20 to check adverse events and TB signs and symptoms since the last dose.

At every physical visit or remote consultation, symptoms and signs of TB disease will be reviewed as well as concomitant medications using a brief questionnaire. There will be no formal study visits after completion of treatment.

### Protocol treatment discontinuation

An individual participant may stop treatment early or trial participation be stopped early for any of the following reasons: Unacceptable toxicity or adverse event including (eg, serious adverse events leading to discontinuation of treatment); intercurrent illness that prevents further treatment; active TB disease; any change in the participant’s condition that justifies the discontinuation of treatment in the clinician’s opinion; pregnancy; inadequate compliance with the protocol treatment that preclude treatment within allowable time-frame in the judgement of the treating physician; and withdrawal of consent for treatment by the participant.

### Outcomes

#### Primary outcome

The primary outcome is adequate treatment adherence, defined as taking ≥90% of allocated doses within the allowable time frame from randomisation (binary outcome). For the primary analyses, treatment adherence is measured using an electronic monitor box

#### Secondary outcomes

The secondary outcome measures are:

Effectiveness: (1) proportion of allocated doses missed over the treatment period (measured using monitor box); (2) proportion of allocated pills missed over the treatment period (measured using pill counts); (3) taking at least 90% of doses and pills over the treatment period (binary outcome assessed using both monitor box and pill counts) and (4) early study treatment discontinuation for any reasonSafety: (1) permanently stop study treatment due to drug-related adverse events (ie, adverse reactions); (2) experience Grade ≥3 adverse events and (3) develop TB disease within 12 months.

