### Objectives

The primary objective of this trial is to assess the effect of novel rifapentine-based regimens (3HP or 1HP) compared with the standard 90-dose daily rifampicin plus isoniazid (3HR), and the effect of additional treatment support compared with routine support, on LTBI treatment adherence.

The secondary objectives are: (1) to evaluate the effect of LTBI treatment and additional treatment support using alternate measures of adherence outcome; and (2) to compare the frequency of adverse events while on treatment for LTBI, and development of TB within 12 months following treatment. Additionally, we will evaluate the process of delivering the adherence intervention and examine intervention fidelity and acceptability as well as the cost-effectiveness of different treatment options and/or additional treatment support.

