### Sample size

The six-arm design allows evaluation of:

The effect of the novel treatment regimens (3HP and 1HP) vs standard-of-care regimen (3HR), under routine treatment support.The effect of additional treatment support vs routine treatment support for each individual regimen.

A total of 920 participants are to be recruited. This provides 80% power for each of the following comparisons:

Arm 3 vs Arm 1—that is, 3HP+routine treatment support vs 3HR+routine treatment support.Arm 5 vs Arm 1—that is, 1HP+routine treatment support vs 3 HR+routine treatment support.Arm 2 vs Arm 1—that is, 3HR+additional treatment support vs 3HR+routine treatment support.Arm 4 vs Arm 3—that is, 3HP+additional treatment support vs 3HP+routine treatment support.Arm 6 vs Arm 5—that is, 1HP+additional treatment support vs 1HP+routine treatment support.

The power calculations assume the following:

70% adherence rate in Arm 1.3HP and 1HP improve adherence rate by 15% (absolute difference) compared with 3HR, respectively, with routine treatment support.^18 23 24^Compared with routine treatment support, additional treatment support improves adherence rate by 15% for 3HR, and 10% for 3HP and 1HP, respectively.^12^Two-sided alpha 5% (see below for type I error considerations).Average number of participants enrolled per household is 2, taking into account the average household size in UK.^25^Intra-class correlation within a household is 0.1

The 70% adherence rate assumed for Arm 1 is based on the 77% LTBI treatment completion rate reported from the Public Health England LTBI testing and treatment database for 2018.^26^

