### Blinding

This is an open-label trial. Blinding of participants and care providers to the allocation group is not relevant since the primary objective of this trial is to examine the effect of shorter or weekly regimens and additional treatment support on treatment adherence.

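### The listed tolerability outcome counts only stops judged drug-related in an open-label regimen comparison; stopping for any adverse event should be listed too

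*Protocol article*

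**What the plan says.** Secondary outcomes lists three safety measures. The first is to "permanently stop study treatment due to drug-related adverse events (ie, adverse reactions"), the second is to "experience Grade ≥3 adverse events", and the third is TB disease within 12 months. Under effectiveness, the same section also lists stopping study treatment early for whatever reason. Table 3 (Safety reporting) makes relatedness to the product part of what an adverse reaction is, so the first measure cannot be scored without a causality judgement.

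Under Blinding the article states "This is an open-label trial" and explains: "Blinding of participants and care providers to the allocation group is not relevant since the primary objective of this trial" is about adherence. It says nothing there about safety outcomes.

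The safety objective (Objectives) is "to compare the frequency of adverse events while on treatment for LTBI, and development of TB within 12 months following treatment". It sets no relatedness condition. The regimen question (Sample size) is "The effect of the novel treatment regimens (3HP and 1HP) vs standard-of-care regimen (3HR), under routine treatment support".

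Protocol treatment discontinuation gives the grounds for stopping. They include unacceptable toxicity or an adverse event, with no relatedness condition, and also "any change in the participant’s condition that justifies the discontinuation of treatment in the clinician’s opinion".

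**The concern.** The reason given for not blinding covers adherence measured by the pillbox. It does not cover an outcome that turns on whether an event was caused by the drug. Many of the expected events that Clinical assessment during follow-up says are checked at each visit (nausea, fatigue, weakness, anorexia) are non-specific, so attribution leaves room for discretion. If the same event is blamed more readily on a new regimen than on the familiar one, or the reverse, the outcome will differ between Arms 3 or 5 and Arm 1 for a reason other than tolerability.

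At stake is how the first safety outcome is read for 3HP and 1HP against 3HR, a comparison of adverse events that the Introduction gives as one purpose of the trial. The comparisons of additional with routine support (Arm 2 vs 1, 4 vs 3, 6 vs 5) have the same regimen on both sides, so familiarity with the drug cannot drive a difference there.

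**Working it through.** **The plan's own figures.** The article gives no expected rate of stopping for adverse events and no share judged drug-related, so there is no stated figure for this outcome to reproduce. The 920 participants are justified on adherence. With a two-sided 5% test, pooled variance, no continuity correction and a design effect of 1 + (2 − 1) × 0.1 = 1.1, power is 84.4% (Arm 3 or 5 vs 1), 80.8% (Arm 2 vs 1) and 82.0% (Arm 4 vs 3, 6 vs 5). The stated 80% therefore stands, and this point does not touch it.

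**Which listed outcomes need a causality judgement**

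- Permanent stop for a drug-related event: yes.
- Grade ≥3 adverse events: no. But they miss lower-grade events that lead to stopping, and they may be sparse, since the Introduction reports none at that grade in the pilot.
- Early stopping for whatever reason: no. But by the listed grounds it also takes in withdrawn consent, inadequate compliance and pregnancy. The trial's interventions are meant to change some of these.
- Permanent stop for any adverse event: not listed.

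**How attribution enters.** Let p be the proportion in an arm who stop permanently for any adverse event, and a the share of those stops called drug-related. The outcome as written has rate p × a, so

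observed risk ratio = (p_new × a_new) / (p_3HR × a_3HR).

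If p is equal in both arms it cancels, and the ratio is a_new / a_3HR whatever the stopping rate.

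**Illustrations (all rates and shares are assumptions)**

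- No true difference, p = 6% in both arms, shares 90% vs 60%: 0.06 × 0.90 = 5.4% against 0.06 × 0.60 = 3.6%, ratio 1.50. For any-event stops the ratio is 1.00.
- No true difference, shares 80% vs 70%: 0.80 / 0.70 = 1.14.
- True difference, p = 8% on a new regimen and 5% on 3HR (ratio 1.60), shares 60% and 90%: 0.08 × 0.60 = 4.8% against 0.05 × 0.90 = 4.5%, ratio 1.07. The difference is nearly hidden.

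**Counts.** Arm sizes are 920 × 5/34 ≈ 135 (Arm 1) and 920 × 6/34 ≈ 162 (Arm 3 or 5). At 6%, stops for any adverse event number about 8 and 10. In the 90% vs 60% case the outcome would show about 5 of 135 against 9 of 162. The standard error of the log risk ratio is √(1/9 − 1/162 + 1/5 − 1/135) ≈ 0.55, which gives an approximate 95% interval of 0.5 to 4.4 around 1.5, ignoring household clustering. With so few events, reclassifying two or three visibly moves the estimate, but the result would not look conclusive by itself.

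**The case against.** The strongest reply has five parts.

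1. **Other outcomes already protect the reader.** Grade ≥3 events and discontinuation for any reason need no causality judgement, and Safety reporting has all adverse events recorded to week 20. This stands as a limit on the harm. A reader might infer that the trial cannot answer its tolerability question. The documents do not support that, because a signal in the first outcome would be read beside these measures. They still do not isolate stopping for an adverse event.

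2. **The alternative is not free of bias.** A reader might infer that counting stops for any adverse event avoids the problem. It does not. The clinician's opinion cited under Protocol treatment discontinuation bears on whether to stop, and that decision and the reason recorded for it remain open label. Only the relatedness judgement is taken out.

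3. **The assessor is not named.** A reader might infer that unblinded clinicians alone decide relatedness. The article does not say so. It abbreviates a full protocol that is not shown and that may provide for independent review. None is described here.

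4. **The mechanism and its direction are not documented.** Every arm combines isoniazid with a rifamycin, and the article gives one list of expected events for all study drugs. This stands: the risk is plausible rather than shown, and it could run either way.

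5. **Drug-related stopping is a defensible measure of regimen toxicity**, and an any-event version could be tabulated later. The first half is fair, and it is a reason to keep the measure. On the second half, the listed outcome is what will be reported as such, and it is narrower than the article's own objective.

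**Conclusion.** The point holds in limited form. As listed, the first safety outcome depends on an attribution judgement that can differ between the new regimens and 3HR, and no listed outcome captures stopping for an adverse event regardless of cause. The effect is confined to the regimen comparisons on one secondary outcome. The primary outcome, the sample size and the support comparisons are untouched.

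The size of the bias cannot be known from the documents. The spurious ratios of 1.14 to 1.5, and the masking of 1.60 to 1.07, rest wholly on assumed stopping rates and attribution shares. They also assume that the decision to stop and the recording of its reason do not themselves differ by arm. This is minor to moderate: an inexpensive improvement to an outcome definition, not an error or a contradiction in the plan.

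**What to change.** List as a safety outcome permanent stopping of study treatment due to any adverse event, regardless of attributed cause. Report the drug-related version beside it as supportive. This changes only how stops are counted, not when treatment is stopped.

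The cost is one line of outcome wording and one supportive analysis. The present outcome already needs the reason for stopping, and adverse events are recorded to week 20, so no new data should be required. Trial status says recruitment had not begun, so the definition can be settled before any data exist. The downside is slight dilution of a true difference by stops for clearly unrelated events; the supportive version lets the reader see how much that matters. The report should say that the any-event outcome still rests on open-label decisions to stop.
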